### Sample size calculations

Using data from the first clusters of blood collection centres that have implemented the ferritin-guided donation intervals, we found a mean increase in ferritin levels of 4 ng/mL (standard deviation (SD) 54 ng/mL) over a 6-month period. To detect a difference of 4 ng/mL, assuming a SD of 54 ng/mL, a two-sided significance level of 5%, a power of 80% and ignoring the correlated observations, a sample size of 5720 subjects is needed. We used the following formula to calculate the actual sample size:
$$ m=\frac{N}{1+\left(n-1\right)\left(1-\rho \right)} $$

where *m* = number of blood collection centres, *N* = sample size ignoring the correlated observations; *n* = average number of subjects within a blood collection centre and *ρ* = intraclass correlation coefficient. Assuming an average number of subject within each blood collection centre of 150 and an intraclass correlation coefficient of 0.1, we need 42 centres in total. With the fixed number of 50 blood collection centres (i.e. 7500 subjects), the power of the study is more than enough to detect the difference of 4 ng/mL. An individual autocorrelation coefficient is not included in our sample size calculation as we include repeated cross-sectional measures. With approximately 7500 donation attempts at fixed collection centres each week, we anticipate that we will be able to collect data on age, sex, Hb levels and deferrals and ferritin levels of approximately 7500 donors at baseline, mid-implementation and after implementation, thereby including more than sufficient data to reliably investigate the effectiveness of the ferritin-guided donation intervals. Furthermore, during data collection at mid-implementation, approximately 3500 donors filled in the questionnaires. We expect about the same response for the data collection after full implementation of the new policy.

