## Method

### Setting

The Sanquin Blood Bank is the only organisation authorised to collect, prepare and distribute blood products, in the Netherlands. All donations are voluntary and non-remunerated. Sanquin consists of 50 fixed blood collection centres, organised into blood collection clusters, 29 in total, distributed over four different topographic regions. Each cluster consists of one to three fixed blood collection centres, some also including mobile collection centres. New donors have to undergo an eligibility test before their first blood donation. This pre-donation screening includes checking of health conditions and risk behaviours by means of a donor health questionnaire and interview, blood pressure and Hb testing and blood sampling for blood typing and infectious disease testing. When eligible, men can subsequently donate a maximum of 5 times/year (minimum donation interval of 56 days) and women a maximum of 3 times/year (minimum donation interval of 120 days).

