The use of a stepped wedge cluster randomised trial approach allows to implement and simultaneously evaluate the policy. As data collection takes place at multiple time points during the implementation period, all blood collection centres contribute data under both the control and intervention condition. Furthermore, this design makes it possible to investigate the effects as if it was a randomised controlled trial by correcting for time and clustering of donors and blood collection centres. This design also introduces some challenges, including prolonged trial duration compared to a standard randomised controlled trial, time-varying confounding, instructing all parties involved, making sure each cluster is committed and performing the assigned policy, and communication with whole blood donors [14, 21]. Furthermore, the lack of blinding to the allocation for both participants and trial staff may introduce a risk of bias [22]. Recruitment bias for the questionnaire data is limited by inviting all eligible donors at the different measurement time points to participate. For other outcomes, all available information from donors who gave consent for their unusable remainder of the donation to be used for medical scientific research was used in the current study. Detection bias is expected to be minimal because outcome assessment does not include any judgement from the researchers [22]. For our sample size calculation, we considered multiple clustering effects that may be present in our study design. An individual autocorrelation coefficient will not affect our sample size as there are no repeated measurements from the same participants. As participants in the same cluster are more alike than participants in another cluster, we included an intraclass correlation coefficient of 0.10. Finally, it may be necessary to take into account a cluster autocorrelation coefficient. However, the cluster autocorrelation coefficient may be difficult to determine and the impact on the total sample size is probably limited [23]. Although the appropriate sample size calculation for stepped wedge designs is still subject of discussion, it is a potential limitation that we did not take into account a cluster autocorrelation coefficient in our sample size calculation. The setting of Sanquin as one organisation with multiple blood collection centres has some advantages in the execution of a stepped wedge cluster randomised trial compared to locally organised general practices or hospitals, for example. The blood collection centres are randomised to implementation steps and instructed to perform the assigned policy, with centralised organisation and monitoring. To our knowledge, this method has never been used in transfusion-related research. The effectiveness of the ferritin-guided donation interval policy on Hb and ferritin levels, Hb deferral rates, donor return rates and donor health likely has a delayed response, because (1) donors’ ferritin levels are only measured when they make a fifth donation and (2) the policy involves donation interval extension which delays follow-up. Delaying the implementation period of ferritin-guided donation intervals should therefore have minimal negative impact on the outcome of the study. Sanquin’s Ethical Advisory board approved the FIND’EM study protocol after the start of the implementation period and we were therefore not able to collect baseline questionnaire data in September 2017. Furthermore, this together with logistic constraints made it impossible to collect data at each implementation step. Therefore, we might have less detailed data on the effects of the new policy on the outcomes over time compared to a design with outcome measurements at each cross-over period. The secondary outcome donor health is measured at mid-implementation and after complete implementation. Investigating the effectiveness of the ferritin-guided donation intervals policy on donor health is limited to the use of questionnaire data collected at mid-implementation and after the implementation period. Data on ferritin levels is available at baseline, mid-implementation and after complete implementation of the policy.

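### The sample-size formula is not valid for a clustered or stepped-wedge design and counts 50 centres where 29 clusters are randomised; the claimed surplus of power for 4 ng/mL is unsupported

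*Protocol article*

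**What the plan says.** Under Sample size calculations, the protocol article takes its planning values from the first clusters to change over: "we found a mean increase in ferritin levels of 4 ng/mL (standard deviation (SD) 54 ng/mL) over a 6-month period". From these it states "a two-sided significance level of 5%, a power of 80% and ignoring the correlated observations, a sample size of 5720 subjects is needed".

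It then applies m = N/[1+(n-1)(1-ρ)], where m is the number of centres, n the subjects per centre and ρ the intraclass correlation. With an average centre size "of 150 and an intraclass correlation coefficient of 0.1, we need 42 centres in total". The conclusion is "With the fixed number of 50 blood collection centres (i.e. 7500 subjects), the power of the study is more than enough". The same section expects about 7500 donors at each of the three measurement points.

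Setting describes the centres as "organised into blood collection clusters, 29 in total". Study design randomises those 29 clusters, and Data analyses puts the random intercept on the cluster. The Discussion says "For our sample size calculation, we considered multiple clustering effects that may be present in our study design". It also concedes that cluster autocorrelation was left out, and adds that the effect on the total is likely to be small.

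**The concern.** The correction for clustering has (1-ρ) where a design effect would have ρ, so an intraclass correlation of 0.1 hardly raises the requirement. Nothing in the formula represents waves, the exposure pattern or a time effect, so it is not a stepped-wedge calculation. Its unit, the centre, is neither the unit randomised nor the unit modelled.

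This is the only quantitative argument in the document that the trial is large enough for its ferritin target. If the surplus does not exist, a reader has been given a wrong idea of how much a non-significant ferritin result would exclude. The formula is also set out in a form that others could copy.

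**Working it through.** **Inputs.** Difference 4 ng/mL, SD 54, two-sided 5%, power 80%, n = 150, ρ = 0.1, 50 centres and about 7500 donors per wave (Sample size calculations). 29 clusters (Setting, Study design). Three waves, with 55% exposed at the middle one (Study population). The first three implementation waves give 8 + 4 + 4 = 16 clusters, and 16/29 = 55%. Exposure is therefore 0, 16 and 29 clusters. Assumed here: 1:1 allocation for the uncorrected N, equal cluster sizes, an immediate full effect, and a range for the cluster autocorrelation (CAC), for which the documents give no value.

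**1. The plan's own figures.** N = 4 × (1.96 + 0.8416)² × 54² / 4² = 5722, which matches 5720 as a total. The printed formula has denominator 1 + 149 × 0.9 = 135.1, and 5720/135.1 = 42.3, stated as 42. The arithmetic reproduces (43 if rounded up, which is trivial with 50 centres available). With 50 centres the formula credits 50 × 135.1 = 6755 independent donors, which would imply 86% power.

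**2. The formula.** It treats a centre of 150 as 135.1 independent donors, a design effect of 150/135.1 = 1.11. Under exchangeable correlation the design effect is 1 + 149 × 0.1 = 15.9, so the effective size is 150/15.9 = 9.4. The two agree only at ρ = 0 and ρ = 1.

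**3. A calculation for the design as run.** Donors per cluster per wave: 7500/29 = 258.6. Total variance 54² = 2916, between-cluster variance τ² = 0.1 × 2916 = 291.6, and residual variance of a cluster-wave mean 2624.4/258.6 = 10.15.

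Write b = τ² × CAC and a = τ²(1 − CAC) + 10.15. With a separate effect for each wave, the 16 early and 13 late clusters differ in exposure only at the middle wave; baseline and final wave act as each cluster's reference. Generalised least squares then gives

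SE² = (1/16 + 1/13) × [a + b − 2b²/(a + 2b)].

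For CAC = 1: a = 10.15, b = 291.6, bracket = 301.75 − 286.61 = 15.14, SE² = 0.1394 × 15.14 = 2.11, SE = 1.45. Power is Φ(4/1.45 − 1.96) = 78.6%. The difference detectable with 80% power is 2.80 × SE.

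| CAC (ICC 0.1) | SE | Power for 4 ng/mL | Detectable difference |
|---|---|---|---|
| 1 | 1.45 | 79% | 4.1 |
| 0.95 | 2.26 | 43% | 6.3 |
| 0.9 | 2.83 | 29% | 7.9 |
| 0.8 | 3.70 | 19% | 10.4 |

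The rows below CAC = 1 are for an analysis that allows for the extra cluster-by-wave variance.

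**4. Linear month term.** Data analyses adjusts for time in months, which may mean a single linear term. Baseline was in September 2017 (Discussion) and the final wave was planned for the end of November 2019 (Trial status), about 26 months later. Exactly 16 clusters were exposed from October 2018 until March 2019, so the middle wave lies at about 13/26 = 50% to 18/26 = 69% of the span. At ICC 0.1 and CAC = 1, power over that range is 79% to 82%.

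**5. Other ICCs, 29 clusters, wave effects.** At CAC = 1, power is 77%, 76% and 77% for ICC 0.01, 0.02 and 0.05. At ICC 0.01 it is 68% for CAC 0.9 and 60% for CAC 0.8.

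**6. Centres or clusters.** At ICC 0.1, power is 78.8% with 50 centres and 78.6% with 29 clusters if CAC = 1. At CAC = 0.95 it is 54% against 43%.

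**The case against.** The strongest reply is that the design itself is close to adequate. The planned model has a random intercept for cluster and nothing else, which is CAC = 1. Under that model power is within about 1.4 points of the 80% target, and with a linear month term it can pass it. That stands: a bad formula has arrived near a tolerable answer, because clusters serve largely as their own controls.

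The steep falls in power need a CAC below 1. The values used here are assumptions, and the Discussion already lists the omission of this coefficient as a limitation. That stands too. What does not stand is the Discussion's view that the effect is probably small: at the plan's own ICC of 0.1, moving CAC from 1 to 0.95 takes power from 79% to 43%.

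It can also be said that the calculation decided nothing, since every fixed centre takes part and all clusters are reported to have changed over. That limits the practical harm, but leaves a printed formula and a conclusion that are wrong as stated.

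A reader might infer more than the documents support:

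- **That 606 centres are needed, or that power is 12%.** These follow from 5720 × 15.9/150 and from 50 × 150 donors in a parallel cluster trial. This trial also uses contrasts within clusters, so neither figure describes it.
- **That power is 36%.** This follows if 7500 is taken as the total over all waves, but the plan expects about 7500 at each.
- **That counting centres instead of clusters is what undoes the power claim.** Under the plan's model it changes almost nothing; it matters only when CAC is below 1.

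**Conclusion.** The point holds in a limited form. The formula is invalid, its unit does not match the randomisation or the model, and the claim of surplus power does not follow from it. Under the plan's own model and ICC, power for 4 ng/mL is about 79% with wave effects and 79% to 82% with a linear month term: about at target, with no margin. The documents do not show that the trial is badly underpowered. They do leave that possibility open, because no CAC is given and power at ICC 0.1 is very sensitive to it.

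These figures assume equal cluster sizes, 7500 donors in every wave and a full, immediate effect. Study population expects the effect to be delayed, so on that account they are on the favourable side.

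**What to change.** - Delete the formula and the 42-centre result ("we need 42 centres in total").
- Restate power, or the detectable difference, with a stepped-wedge variance formula for 29 clusters, about 259 donors per cluster per wave, three waves and exposure 0/16/29. State the form of the time term, and show a range such as ICC 0.01 to 0.1 and CAC 0.8 to 1.
- Replace the claim of ample power with the resulting figures.
- In the Discussion, revise the remark that autocorrelation matters little, and the statement that several clustering effects were considered.

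The CAC should not be estimated from baseline haemoglobin: one cross-section cannot identify a correlation between periods, and haemoglobin correlations are not ferritin correlations.

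The cost is rewriting one section and a few sentences of the Discussion, and a less favourable stated power. Enrolment does not change.

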### Data analyses

Descriptive statistics will be provided for the donor population at baseline, mid-implementation and after full implementation. Linear mixed models (i.e., multilevel analysis) will be used to investigate differences in Hb and ferritin levels, low-Hb deferral, donor return rates and donor health between intervention and control groups using data collected at baseline, mid-implementation and after implementation. Two-level models with donors nested within blood collection clusters will be fitted, with a random intercept for cluster to adjust for the correlation between measurements of donors within the same cluster. All models include a binary variable indicating whether the observation was done before or after the start of the intervention and will be adjusted for the time point of implementation of the policy (fixed variable, time in months since the start of implementation period). Because of the nature of our outcome measures and because we include a new sample of donors at every measurement time point, we do not expect robust methods to be appropriate for sensitivity analyses. To investigate how the impact of ferritin-guided donation intervals develops over time, the latter will also be included as an effect modifier [14]. An intention-to-treat approach will be used and stratified analyses will be performed to investigate differences in the effectiveness of ferritin-guided donation intervals for male and female donors.

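### The planned model has no term for the blood collection centre, although the trial is sized by centre; intervals may be too narrow if the mix of centres within clusters shifts between measurement weeks

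*Protocol article*

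**What the plan says.** All places are in the protocol article.

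- **Setting:** there are 50 fixed centres in 29 clusters. "Each cluster consists of one to three fixed blood collection centres".
- **Study design:** the cluster is the randomised unit.
- **Study population and Data collection:** there are three measurement time points (waves below), each a single pre-selected week with a new sample of donors. Questionnaires are collected only at the second and third.
- **Sample size calculations:** *n* is the "average number of subjects within a blood collection centre", set at 150. The ICC is 0.1 and the result is 42 centres, so the unit counted is the centre.
- **Data analyses:** "Two-level models with donors nested within blood collection clusters will be fitted, with a random intercept for cluster". On a fallback for standard errors: "we do not expect robust methods to be appropriate for sensitivity analyses".
- **Discussion:** the design is said to permit inference by "correcting for time and clustering of donors and blood collection centres". A few sentences later the ICC of 0.10 is explained by the resemblance of participants who share a cluster.

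**The concern.** The sample size places the correlation in the centre. The model places it in the cluster. The Discussion supports either reading. The levels differ wherever a cluster has two or three centres.

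The policy effect is estimated largely from changes within clusters over time. A constant difference between two centres of one cluster cancels from that comparison only while each centre keeps its share of the cluster's donors. If one centre opens fewer days in a given week, draws fewer donors or returns fewer questionnaires, the cluster mean moves although nothing has changed in either centre. A model without a centre term counts that movement as information about time or policy. At stake are the coverage of the intervals, the false-positive rate and some precision. No sandwich-type check is planned that might reveal the problem.

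**Working it through.** **1. The plan's own figures.** The inputs are a difference of 4 ng/mL, SD 54, two-sided 5% and 80% power. Per arm: 2 × (1.960 + 0.842)² × 54² / 4² = 2 × 7.849 × 182.25 = 2861, so 5722 in total; the plan says "a sample size of 5720 subjects is needed". Its formula gives 5720 / (1 + 149 × 0.9) = 5720 / 135.1 = 42.3 centres, printed as 42. The arithmetic reproduces, and the unit is the centre. This does not endorse the formula.

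**2. Mechanism by hand.** Take a cluster of two equal centres with 150 donors each per week, and assume the whole ICC of 0.1 lies between centres.
- Centre SD: 54 × √0.1 = 17.1 ng/mL. SD of the difference between the two centres: 17.1 × √2 = 24.1.
- Let each centre's weekly count vary with a log-SD of 0.3. The centre's share then varies with SD 0.5 × 0.5 × 0.3 × √2 = 0.106.
- The cluster mean moves by 0.106 × 24.1 = 2.56 ng/mL (SD).
- Sampling SE of the cluster-week mean: 54 × √0.9 / √300 = 2.96.
- True over sampling-only SE: √(2.96² + 2.56²) / 2.96 = 1.32.

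With a log-SD of 0.1 the movement is 0.85 and the ratio is 1.04. With a centre ICC of 0.02 and a log-SD of 0.3, the movement is 0.106 × 10.8 = 1.15, the sampling SE is 3.09 and the ratio is 1.07. Questionnaires have 3500 / 50 = 70 responders per centre, so the sampling SE is 51.2 / √140 = 4.33 and the ratio at 0.3 is √(4.33² + 2.56²) / 4.33 = 1.16. The same shift matters less there because sampling error is larger. Clusters with one centre are unaffected.

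**3. Whole trial, by simulation.** Documented inputs: 29 clusters, 50 centres, 8 + 4 + 4 = 16 clusters exposed at mid-implementation (16/29 = 55%) and all at the end; about 7500 donors in each of three waves for ferritin and Hb, and about 3500 in each of two waves for questionnaires. Assumed inputs: 13, 11 and 5 clusters with one, two and three centres (13 + 22 + 15 = 50), the size of the shift, and the whole ICC of 0.1 at centre level. Each cell gives true SE / model SE and 95% interval coverage under the two-level model.

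| Shift (log-SD) | Ferritin, Hb | Questionnaires |
|---|---|---|
| Sampling variation only | 0.98; 95.1% | 0.99; 95.4% |
| 0.1 | 1.01; 94.8% | 1.01; 94.6% |
| 0.3 | 1.29; 86.8% | 1.08; 92.9% |
| 0.5 | 1.59; 78.4% | 1.28; 87.2% |

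With a centre intercept, coverage is 94.3-95.5% in every cell. A shorter run gave 1.16 for questionnaires at 0.3, so that cell is uncertain, but it stays below the ferritin figure.

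A second simulation for ferritin (12, 13 and 4 clusters; coefficient of variation of centre-week counts in place of log-SD) gave 1.56 / 1.45 = 1.08 at 15% and 1.81 / 1.44 = 1.26 at 30%. The reported SE is then 1 − 1.44/1.81 = 20% too small.

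**4. Sensitivity at a shift of 0.3.** With half the ICC at centre level, the ratios are about 1.13 (ferritin) and 1.03 (questionnaires). With an ICC of 0.02, all at centre level, they are about 1.03 and 1.05. Other cluster layouts (8/21/0 and 18/1/10) give 1.23 and 1.08-1.11. With a centre ICC of 0.01 the false-positive rate in the second simulation stays at 5.0%.

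**5. Questionnaires with unequal response.** Assume response of 47% (3500/7500) varying by 15 percentage points (SD) between centre-weeks, counts varying by 15%, and two waves. The ratio is 1.20 with 9.7% false positives if the whole ICC is at centre level, and 1.08 with 6.9% if half is. Centre intercepts bring these to 4.9% and 4.2%.

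**The case against.** The strongest reply is that leaving out the centre does no harm in itself. With a stable mix the centre effects average into the cluster intercept and coverage is nominal. No passage reports or predicts a shift: all 50 centres are sampled each time, and similar questionnaire response is expected. This stands, and the point is conditional for that reason. A reader might infer that the intervals are certainly too narrow; the documents do not support that.

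A reader might also infer that questionnaire outcomes suffer most. At an equal shift and ICC 0.1 the order is the reverse. It would hold only if the responder mix shifts more than attendance. Partial response makes that possible, but no response by centre is given.

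A random intercept for the randomised unit is conventional, and the Discussion's wording on clustering can be read as meaning the clusters of centres. That also stands, so the Discussion is not proof of a broken promise. The conflict over the level of the ICC remains.

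A shifting mix looks like cluster-by-wave variation, so a cluster-by-wave effect would absorb much of it. In simulation, adding only that effect cut false positives from 7.1% to 6.0% (15% shift), from 13.3% to 7.1% (30%) and from 9.3% to 5.6% (two-wave questionnaires). If such a term is adopted, a centre intercept adds mainly precision. The stated model, however, has neither.

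Finally, an analysis plan that is not shown might add levels. But the article does not leave the structure open: it names the number of levels and the random effect.

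**Conclusion.** The point holds in conditional form. The stated model omits the level used to size the trial, and the article is inconsistent about the level to which the ICC of 0.1 belongs. Harm requires both a shift in centre shares between waves and a material centre component of the ICC. With the whole 0.1 at centre level, shifts of about 10-15% put the true SE 1-8% above the reported SE. Shifts of about 30% put it 26-29% above, with the reported SE about 20% too small and coverage about 87%. With a centre ICC of 0.01-0.02 the effect is small or absent.

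The cluster layout, the size of the shift and the centre's share of the ICC are assumptions; the article gives none of them. The calculations are for continuous outcomes and were not repeated for deferral or donor return.

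This is not the largest threat to the model. With an assumed cluster-by-wave variance of 1% of the total and a stable mix, coverage falls to 66% (ferritin) and 80% (questionnaires). A centre intercept alone leaves it at 64% and 79%.

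**What to change.** - In Data analyses, add an intercept for centre, either random and nested in cluster or fixed, to the models for all outcomes. Keep the policy indicator at cluster level.
- State the ICC at the same level in Sample size calculations and in the Discussion, and say which level is meant.
- Decide on a cluster-by-wave random effect separately. The centre intercept does not replace it.
- Report donor and responder numbers by centre and wave, so that readers can see whether the mix moved.

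The cost is one extra variance component. Sampling is by fixed centre, so the centre of each visit should already be on record and no new data are needed. If the mix proves stable, the results will hardly change.

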### Study population

Both new (i.e. a donor undergoing pre-donation screening) and repeat donors (i.e. a donor making a whole blood donation or attempt) are eligible to participate in this study. The intervention likely results in delayed effects. Ferritin levels of a donor visiting a blood collection centre where the intervention has been implemented will only be measured every fifth donation. Furthermore, the extension of donation intervals makes it necessary to allow the blood collection centres to be exposed to the intervention for a certain amount of time before donors return and the effectiveness of the new policy becomes observable. We therefore selected three measurement time points: (1) before implementation (i.e. baseline), (2) mid-implementation (when 55% of blood collection centres had implemented the policy) and (3) after complete implementation of ferritin-guided donation intervals. As Sanquin had already started the implementation of the ferritin-guided donation intervals in November 2017, before approval from the Ethical Advisory Board for the FIND’EM study, we were unable to collect questionnaire data from donors at baseline. However, baseline data on other outcomes (Hb and ferritin levels, low-Hb deferral and donor return) are measured after ethical approval in stored samples, and a large majority of the donors (99%) provide their consent to the routine request to ‘make the unusable remainder of my donation available for medical scientific research in general’ (Fig. 2). Whole blood donors who visit one of the 50 fixed blood collection centres during a pre-selected week at mid-implementation or after complete implementation are asked to participate by completing questionnaires. This makes the current study an open cohort design study with repeated cross-sectional measures and new samples at each measurement. Donors registering at the registration desk of one of the collection centres during one of these time points will receive a leaflet with information on why this study is performed, explaining that upon participation, the donor is asked to fill in a questionnaire and participation is voluntary, the leaflet contains contact details of the research team in case of any questions and a link to the study website with additional information and frequently asked questions. The donor is asked to read the study information while waiting for their health check. After the check, the donors will be asked whether they have read the study information. If the donor decides to participate, an informed consent form will be signed and the donor physician or nurse will sign the form as a representative of the researcher. Donors who decide not to participate are asked to write down the reason for non-participation.

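### The analysis model assumes, without justification, that clusters do not shift relative to one another between waves; at the plan's ICC of 0.1 even modest drift would inflate the type I error

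*Protocol article*

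**What the plan says.** Under Data analyses, the protocol article nests donors within blood collection clusters and fits the model "with a random intercept for cluster to adjust for the correlation between measurements of donors within the same cluster". No cluster-by-wave term is named. Time enters as a "fixed variable, time in months since the start of implementation period" and also as an effect modifier of the intervention. Both time terms are fixed and shared by all clusters. The models are fitted "using data collected at baseline, mid-implementation and after implementation".

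On sensitivity analyses, the same section says that "we do not expect robust methods to be appropriate for sensitivity analyses". It gives two reasons: the nature of the outcomes, which is not explained, and the fact that each wave draws a new sample of donors.

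The Discussion returns to clustering only for the sample size. It says that a cluster autocorrelation may have to be considered, then that "the cluster autocorrelation coefficient may be difficult to determine and the impact on the total sample size is probably limited", and it lists the omission as a potential limitation. The point is not carried into the analysis model.

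**The concern.** With one random intercept per cluster, two donors from the same cluster are taken to be equally correlated whether they attended in the same week or at waves about 26 months apart (September 2017 to the end of November 2019). That is CAC = 1. If a cluster's mean moves between waves for local reasons, such as a change in donor mix, the model treats the movement as independent donor noise and averages it over all donors in the cell. With some 259 donors per cell it almost vanishes from the standard error, while it stays in full in the actual error of the estimate.

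The reason given for setting robust methods aside does not meet this. New donors at each wave remove correlation within a person. They leave the correlation between different donors of the same cluster and wave, which is the one at issue. Cluster-robust and permutation inference both apply to repeated cross-sections.

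At stake is whether the reported confidence intervals have their stated coverage, in a trial meant to guide policymakers.

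**Working it through.** **Inputs from the protocol article**
- Clusters: "organised into blood collection clusters, 29 in total" (Setting).
- Donors: "ferritin levels of approximately 7500 donors at baseline, mid-implementation and after implementation" (Sample size calculations). Per cluster-wave, 7500/29 = 258.6.
- Middle wave: 55% of centres had crossed over (Study population). This matches 16 of 29 clusters (8 + 4 + 4, Study design).
- SD 54 ng/mL, target difference 4 ng/mL, ICC 0.1, two-sided 5% (Sample size calculations).
- Questionnaires: about 3500 respondents in each of two waves; 3500/29 = 120.7 per cluster-wave.

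**Assumption.** The CAC is not given. The range 0.80 to 1.00 is shown.

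**1. The plan's own figures.** Ignoring correlation, N = 2 × 2(1.96 + 0.842)² × 54²/4² ≈ 5722, against 5720 stated. The printed formula gives 5720/(1 + 149 × 0.9) = 42.3, against 42 stated. That calculation has no wave structure and no CAC. The article states no type I error for the mixed model, so there is no plan figure to reproduce on this point.

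**2. Variance components.** The total variance is 54² = 2916, split as
- cluster: ICC × CAC × 2916
- cluster-by-wave: ICC × (1 − CAC) × 2916
- donor: (1 − ICC) × 2916 = 2624.4 at ICC 0.1, or 2624.4/258.6 = 10.15 for a cell mean.

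The cluster-by-wave part does not shrink with the number of donors in a cell. At CAC 0.95 it is 0.1 × 0.05 × 2916 = 14.58, already more than the 10.15 of donor noise.

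**3. Understatement of the standard error.** With large cells,

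true SE / model SE ≈ √[1 + m × ICC × (1 − CAC)/(1 − ICC)], and type I error = 2[1 − Φ(1.96 / ratio)].

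At ICC 0.1 and CAC 0.90: √[1 + 258.6 × 0.1 × 0.1/0.9] = √3.87 = 1.97, and 2[1 − Φ(0.996)] = 32%.

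The full generalised least squares calculation (29 clusters, 3 waves, 16 treated at the middle wave) agrees:

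| CAC (ICC 0.1) | Cluster-by-wave variance | Model SE, ng/mL | True SE, ng/mL | Type I error |
|---|---|---|---|---|
| 1.00 | 0 | 1.45 | 1.45 | 5% |
| 0.98 | 5.83 | 1.45 | 1.82 | 12% |
| 0.95 | 14.58 | 1.46 | 2.26 | 21% |
| 0.90 | 29.16 | 1.46 | 2.85 | 32% |
| 0.80 | 58.32 | 1.46 | 3.76 | 45% |

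Linear and categorical time give the same rates.

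**4. Other settings (type I error)**

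| Setting | CAC 0.95 | CAC 0.90 | CAC 0.80 |
|---|---|---|---|
| ICC 0.05 | 13% | 20% | 31% |
| ICC 0.02 | 8% | 11% | 17% |
| ICC 0.01 | 6% | 8% | 11% |
| Questionnaires, ICC 0.1 | 13% | 19% | 30% |
| One sex, about half of each cell, ICC 0.1 | 13% | 21% | 31% |

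**5. Check by simulation.** Over 1500 simulated trials per scenario with no effect, analysed by REML with a random intercept only, rejection at ICC 0.1 was 5.7% at CAC 1, 32.9% at 0.90 and 45.2% at 0.80. At ICC 0.01 and CAC 0.80 it was 10.2%. In a separate set of 500 runs per scenario, unequal cluster sizes (coefficient of variation 0.5) gave 31% at ICC 0.1 and CAC 0.90.

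**6. Effect of the remedy.** In the 500-run set, adding a random cluster-by-wave effect brought rejection to 3% to 8% in every scenario where that model was checked, and to 3% to 7% with a t reference. Monte Carlo error is about 1 percentage point.

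**7. Power.** With the cluster-by-wave variance in the model, power for 4 ng/mL at ICC 0.1 is Φ(4/SE − 1.96):
- CAC 1: SE 1.453, power 79%
- CAC 0.95: SE 2.258, power 43%
- CAC 0.90: SE 2.834, power 29%

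**The case against.** The strongest reply is that the inflation comes from the CAC, which the documents do not supply. At CAC 1 the planned model holds its level. This stands: a reader might infer that the model will produce false-positive rates of 10% to 45%, and the documents do not support that as a statement of fact. At ICC 0.01 with CAC 0.95 to 0.90 the rate is only 6% to 8%.

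The extreme case also asks a lot. ICC 0.1 with CAC 0.80 means that each cluster's mean ferritin moves at each wave with an SD of 54 × √(0.1 × 0.2) = 7.6 ng/mL, nearly twice the target difference. Collection is run by one organisation with central monitoring, ferritin is measured on one named analyser, and Hb on one named device. These facts argue against large drift. They do not establish that there is none, since donor mix can still change locally. At ICC 0.1, a CAC of 0.98 is enough to more than double the nominal rate.

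A reader might also apply the main figures to every outcome. Questionnaires and sex-stratified analyses have smaller cells and less inflation, and the binary outcomes were not simulated.

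Nor does the Discussion claim that the type I error is unaffected. Its remark concerns sample size, rests on a cited source that is not available here, and is followed by an admission of a limitation.

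Finally, degrees-of-freedom methods are often left to an analysis plan, which is not shown. That is fair, but the random-effects structure and the dismissal of robust methods are both stated in the article.

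**Conclusion.** The point holds in conditional form. The article fixes a model that assumes CAC = 1, offers no evidence for it, and sets aside the methods that could guard against a departure, for a reason that does not bear on the correlation concerned. If clusters are perfectly stable relative to one another, nothing is lost. If they are not, standard errors are too small by a factor that depends on the ICC and CAC: at the plan's ICC of 0.1, about 1.25 at CAC 0.98 and about 2.6 at CAC 0.80; at ICC 0.01 and CAC 0.80, about 1.2.

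These figures assume a continuous outcome and about 259 donors in each cluster-wave. The expectation that the CAC matters little for the sample size is also not borne out at the plan's own ICC, where power for 4 ng/mL falls from about 79% to 43% as the CAC goes from 1 to 0.95.

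**What to change.** - Add a random cluster-by-wave effect to the models. There are 29 × 3 = 87 cells (29 × 2 = 58 for the questionnaires). Use a small-sample t reference suited to 29 clusters. If the term is left out, justify CAC = 1.
- Remove the statement that robust methods are not appropriate because each wave is a new sample. A small-sample cluster-robust variance, or a permutation test that re-draws the region-constrained allocation, may serve as an optional sensitivity check.
- In the Discussion, state that a CAC below 1 can materially reduce power, with the figures for 4 ng/mL at ICC 0.1: about 79% at CAC 1, 43% at 0.95 and 29% at 0.90.

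The cost is one further variance term and some rewording, with no new data and no change of design. Intervals will be wider if clusters do drift, and little is lost if they do not.
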